### Planned Analysis

A statistician independent of the research team will analyze the data. Data will be analyzed on an intention-to-treat basis. Descriptive statistics (mean, SD, and frequency) will be calculated. Univariate and multivariate statistical assumptions will be examined and managed according to recommendations by Tabachnick and Fidell [33]. Mixed linear effects models will be used to assess between-group differences across time. All primary and secondary study outcomes will be analyzed similarly. Follow-up mean comparisons and Cohen *d* effect sizes will used to examine differences between individual time study points. Two rounds of analyses will occur: the primary outcome (body mass) and key secondary outcomes (blood variables, surveys, app data) will be assessed at the 12 weeks and follow-up exploratory analyses will be performed after 24 and 48 weeks. An additional exploratory mixed effects model using all daily body mass measures during the first 12 weeks will examine whether the patterns of body mass change differ between the 2 study groups.

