**Primary outcome**				
	Bodyweight scale	Change in body mass (in kilograms)	12 weeks	Those in the Keyto intervention arm will achieve greater weight loss at 12 weeks than those in the Weight Watchers arm.

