### Sample Size Calculation

There are no known studies with protocol design as we describe. Thus, the amount of weight loss expected with a hands-off self-monitoring ketogenic mHealth application is not known. Thus, we determined sample size in order to detect a clinically meaningful 5% difference in weight loss, assuming a mean body mass of 100 kg with a standard deviation of 15 kg [32]. A 5% weight loss corresponds to a small-to-moderate effect size (Cohen *d*=0.33, *f*=0.165). Using G*Power software (version 3.1.9.3) a total sample size of 124 is required to detect a between groups effect with 80% power and α=.05 with 2 groups and 2 time points (primary outcome at 12 weeks) assuming a correlation among repeated measures of *r*=0.75. In order to preserve power and account for 15% loss to follow-up, we will aim to recruit 144 participants (ie, n=72 per group).

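### The sample size is powered for a general between-group effect, but the primary hypothesis is a week-12 difference in weight change; naming the baseline-adjusted week-12 contrast reconciles them and raises power from about 75% to 80%

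*Protocol article*

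**What the plan says.** Table 1 of the protocol article gives the primary outcome as change in body mass in kilograms at 12 weeks, with this hypothesis: "Those in the Keyto intervention arm will achieve greater weight loss at 12 weeks than those in the Weight Watchers arm".

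The Sample Size Calculation starts from a 5% target, "we determined sample size in order to detect a clinically meaningful 5% difference in weight loss", and proceeds "assuming a mean body mass of 100 kg with a standard deviation of 15 kg". It converts this to d = 0.33 and f = 0.165, takes a correlation of 0.75 between repeated measures, two groups and two time points, and concludes that "a total sample size of 124 is required to detect a between groups effect with 80% power". Recruitment is raised to 144 (72 per arm) for 15% loss to follow-up.

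Planned Analysis states: "Mixed linear effects models will be used to assess between-group differences across time". It then adds: "Follow-up mean comparisons and Cohen *d* effect sizes will used to examine differences between individual time study points". The 24- and 48-week analyses and the daily-weight model are labelled exploratory. Body mass is measured at baseline, but the analysis text does not say how baseline enters the primary comparison.

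**The concern.** Three sections describe the primary comparison in three ways. Table 1 hypothesises a difference in change at week 12. The sample size section plans "to detect a between groups effect with 80% power" over two time points; in repeated-measures terms this is the between-factors (arm) effect, which averages baseline with week 12. Planned Analysis speaks of group differences over time, most naturally the arm-by-time term.

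These tests do not have the same power, and the powered effect is not the hypothesised one. The stated 80% therefore cannot be attached to the test a reader would expect to see. Baseline weight, which the trial collects anyway and which is assumed to correlate 0.75 with week 12, may also enter the analysis only by subtraction, which gives away power.

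**Working it through.** **Inputs (Sample Size Calculation).** Difference δ = 5% of 100 kg = 5 kg; SD σ = 15 kg; r = 0.75; f = 0.165; power 80%; α = 0.05; N = 124, so n = 62 per arm. Assumptions added here: α is two-sided, and the single SD given applies at both time points.

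**1. Reproducing 124.** For a baseline-adjusted comparison, the residual SD is σ√(1 − r²) = 15 × √0.4375 = 9.92 kg. Then n per arm = 2 × (1.960 + 0.842)² × 9.92² / 5² = 2 × 7.849 × 98.44 / 25 = 61.8, so 62 per arm and **124 in total**. This is the normal approximation. An F test with N − 3 degrees of freedom gives 126 with f = 1/6 and 130 with the rounded f = 0.165.

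**2. The test the sample size text appears to describe.** For a repeated-measures between-factors F test with m = 2 measurements, the noncentrality is λ = f²Nm / (1 + (m − 1)r). At N = 124, λ = 0.165² × 124 × 2 / 1.75 = 3.86 on 1 and 122 degrees of freedom, which gives power **0.50**. Reaching 80% needs N = **256**.

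**3. Other tests tried against 124.** Change score: 142 (normal approximation) to 148 (F test). Week-12 values alone: 284 to 292. Within-between interaction with the same f: 40. None gives 124.

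**4. Power of the two tests that fit Table 1, at 62 per arm.**

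| Contrast | SD (kg) | SE = SD × √(2/62) | 5 / SE | Power, normal (t) |
|---|---|---|---|---|
| Arm-by-time change | 15 × √(2 × 0.25) = 10.61 | 1.905 | 2.62 | 0.747 (0.740) |
| Week 12 adjusted for baseline | 9.92 | 1.782 | 2.81 | 0.801 (0.795) |

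If all 72 per arm were analysed, the normal figures would be 0.807 and 0.856. The ratio of the two variances is (1 − r²) / (2(1 − r)) = (1 + r)/2 = 0.875, so adjustment removes 12.5% of the variance at r = 0.75. The gain shrinks as r rises (ratio 0.975 at r = 0.95).

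**5. Type I error.** One test fixed in advance: 0.05. If the test were picked after seeing the data, simulation under no effect (400,000 draws, r = 0.75, 62 per arm) gives:

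- change or baseline-adjusted: 0.066
- arm main effect or change: 0.097 (exactly 1 − 0.95² = 0.0975, as the two are uncorrelated at equal SD)
- arm main effect, change or raw week-12 means: 0.109, with a range of 0.099 to 0.112 for r from 0.5 to 0.95 and week-12 SD from 15 to 16.5 kg

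**The case against.** Table 1 fixes the outcome, the time and the direction. That excludes an arm main effect averaged over baseline, raw week-12 means and within-arm comparisons as tests of the primary hypothesis. Read with Table 1, the mixed-model sentence points to arm-by-time change. The mean comparisons are called follow-up, so they read as subordinate; if they were examined only after a significant arm-by-time test, the error would stay at 0.05. An independent statistician does the analysis. The exact model term and the handling of baseline are commonly left to an analysis plan, which is not shown here. All of this stands, and the unnamed contrast alone would not be a finding.

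It also disposes of a stronger reading. A reader might infer that the plan roughly doubles the false-positive rate, or that a true 5 kg effect would be reported as 2.5 kg and detected only 17% of the time. The first needs a rule that a win on any test counts, and the article contains no such rule. The second needs the arm main effect to be the reported primary estimate, and no section says so.

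Two things survive. The sample size text names an effect that is not the hypothesised one and does not reproduce its own number, and an unseen analysis plan cannot change that wording. Nor is baseline adjustment only a matter of taste: with complete data at two time points and unconstrained baseline means, the arm-by-time term equals the change-score contrast. Under the article's own inputs it falls short of the stated 80%.

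**Conclusion.** The point holds as a mismatch between the powered effect, the hypothesis and the planned model, not as an inflation of type I error. At 62 per arm, the natural reading of Planned Analysis has about 74-75% power and the baseline-adjusted week-12 difference about 80%. The between-factors effect has about 50% at N = 124. The stated 124 and 80% agree, to the normal approximation, only with the baseline-adjusted contrast among the tests tried. An increase in error to about 0.07 or 0.11 is conditional on the test being chosen after the data are seen. The figures rest on a two-sided α, equal SDs of 15 kg at both times and r = 0.75. The case for correction is moderate: the remedy is cheap and improves power at no cost in participants.

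**What to change.** In Planned Analysis, name one primary test: the Keyto minus WW difference in body mass at week 12, adjusted for baseline body mass, two-sided at 0.05 with a 95% confidence interval. Fit it either as a mixed model with baseline means constrained equal across arms or as a model with baseline as a covariate. State that the follow-up mean comparisons and Cohen d are supportive and cannot carry the primary claim.

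In the Sample Size Calculation, replace the between-group effect with this same contrast, for which 124 at 80% power is correct by the normal approximation, and state that the test is two-sided.

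The cost is a few sentences, with no further data or participants. The follow-up comparisons lose any confirmatory status. The article reports 49 enrolled in April 2020 and expects the primary phase to finish in October 2020, so on its own timeline the wording can be settled before the week-12 analysis.

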**Manipulation checks**				
	Questionnaires			
		Food attitude survey	12, 24, and 48 weeks	We will examine all baseline questionnaires as potential covariates. We will also examine differences in questionnaire measures between the 2 groups at 12, 24, and 48 weeks.
		Cravings, mood, and energy	Weekly	
		Self-reported dietary adherence	Weekly	
		Pittsburgh Sleep Quality Index	12, 24, and 48 weeks	

^a^HbA_1_c: hemoglobin A_1_c.

^b^HOMA-IR: homeostasis model assessment of insulin resistance.

^c^HDL: high-density lipoprotein.

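### No baseline adjustment is named for body mass, blood or dietary outcomes; under the usual unconstrained mixed model primary power is about 73%, against about 79% when baseline is conditioned on

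*Protocol article*

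**What the plan says.** Under Planned Analysis the protocol article states: "Mixed linear effects models will be used to assess between-group differences across time. All primary and secondary study outcomes will be analyzed similarly". It does not say whether the baseline value is a response, a covariate, or a response with a common mean in both arms.

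The Sample Size Calculation section describes a design "with 2 groups and 2 time points (primary outcome at 12 weeks) assuming a correlation among repeated measures" of 0.75. If week 12 is one of the two time points, the other can only be baseline. The target is a "clinically meaningful 5% difference in weight loss, assuming a mean body mass of 100 kg with a standard deviation of 15 kg", and the result is a total of 124, raised to 144 for 15% loss.

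Table 1 defines the primary outcome as change in body mass at 12 weeks and describes the blood and energy-intake outcomes as changes from baseline. On covariates it says, in the rows for manipulation checks: "We will examine all baseline questionnaires as potential covariates". Baseline body mass, blood values and nutrient intakes are not named as covariates anywhere in the article.

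**The concern.** Taken together, these places most naturally describe a repeated-measures model with baseline on the outcome side. In the usual unconstrained version each arm has its own mean at baseline and at week 12. With complete data, the arm-by-time contrast then equals the difference between arms in mean change. That contrast is always less precise than one that conditions on baseline, unless the correlation is 1.

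Two things are at stake. Precision already paid for would be lost, on the primary outcome and more so on secondary outcomes with weaker baseline correlation, since the same approach is carried over to all of them. And the power statement would not match the test: the planned number would give less than the stated 80%.

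**Working it through.** **Inputs.** From Sample Size Calculation: difference 5 kg (5% of 100 kg), SD 15 kg, r=0.75, alpha 0.05, power 80%, total 124 evaluable, 144 recruited, 15% loss. Sidedness is not stated; two-sided is assumed. Expected completers: 144 × 0.85 = 122.4, about 61 per arm.

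**SD of each contrast.**
- Change score: 15 × √(2(1 − 0.75)) = 10.61 kg, variance 112.5.
- Conditioned on baseline: 15 × √(1 − 0.75²) = 9.92 kg, variance 98.4.
- Variance ratio: (1 − r²)/(2(1 − r)) = (1 + r)/2 = 0.875, that is, 12.5% lower when baseline is conditioned on.

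**Reproducing the plan's 124.** By the normal approximation, n per arm = 2 × (1.960 + 0.842)² × variance / 5² = 0.628 × variance.
- Conditioned on baseline: 0.628 × 98.4 = 61.8, so 62 per arm, total 124. This matches the plan. With the t distribution the total is 126.
- Change score: 0.628 × 112.5 = 70.6, so 71 per arm, total 142. With the t distribution the total is 144.
- Week-12 value alone: total 284.
- Repeated-measures F tests with f=0.165, two measurements and r=0.75: total 256 for the between-groups effect, 40 for the within-between interaction.

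Of these two-sided variants, only the baseline-conditioned variance gives 124.

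**Power for 5 kg** (noncentral t, noncentrality 5/(SD × √(2/n)), one degree of freedom fewer with the covariate):

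| Per arm | Change score | Conditioned on baseline |
|---|---|---|
| 61 (144 less 15%) | 73.3% | 78.8% |
| 62 (the planned 124) | 74.0% | 79.5% |
| 72 (no loss) | 80.2% | about 85% |

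For 61 per arm, √(2/61) = 0.181, so the noncentrality is 5/(10.61 × 0.181) = 2.60 against 5/(9.92 × 0.181) = 2.78.

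**Sensitivity to r** (61 per arm, change score then conditioned): r=0.5, 44.7% to 55.9%; r=0.75, 73.3% to 78.8%; r=0.9, 98.3% to 98.7%; r=0.95, no visible gain.

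**Secondary outcomes.** The article gives no correlations, so r is an assumption here. By 1 − (1 + r)/2, conditioning lowers the variance relative to a change score by 35% at r=0.3, 25% at r=0.5 and 15% at r=0.7. Relative to the follow-up value alone, the change-score variance is 2(1 − r): at r=0.3 that is 1.4, or 40% more. Below r=0.5 a change score is noisier than ignoring baseline.

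**The case against.** The strongest reply is that the unconstrained form is an inference. The Planned Analysis sentence fits equally well with a model of follow-up values that has baseline as a covariate, or with a common baseline mean, and neither carries change-score noise. The two time points describe a power-software input, not a fitted model. An article may leave such detail to a full protocol or analysis plan. This stands as far as it goes: a reader might infer that the plan commits to change scores and that its true power is 73%, and the documents do not establish that. What the objection does not remove is that the stated description points to baseline as a response, while the stated sample size needs the variance of a baseline-conditioned analysis.

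A reader might also infer that baseline values are never covariates for any outcome. That goes too far. Table 1 makes all baseline questionnaires candidates, and Planned Analysis counts surveys among the key secondary outcomes. Nor does the two-point formula apply to every comparison: single-time-point mean comparisons and a daily-weight model are also planned.

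Third, it can be said that 79% is no bonus over the plan, because 124 already matches an adjusted analysis. That is right, and it makes the point one of matching the analysis to the number. It does not prove that adjustment was intended.

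Finally, adjustment is not quite free for body mass. Study materials are mailed after randomization, the scale is connected during each arm's onboarding, and the Body Mass section allows a baseline averaged over a week. Such a baseline could include days on the diet, and conditioning on it, or constraining it to be equal, could then bias the arm difference. This stands and shapes the fix.

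**Conclusion.** The point holds in a limited form. The article describes baseline as one of the repeated measurements and names no baseline body mass, blood or dietary covariate. If the usual unconstrained model is fitted, the 12-week contrast has about 73% power at the expected 61 completers per arm; conditioning on baseline gives about 79%, close to the stated 80%. A change-score test would need 142 to 144 evaluable participants, not 124.

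These figures rest on the plan's own 5 kg, SD 15 kg and r=0.75, on a two-sided test, and on complete data at two time points. The gain is material at r=0.75, larger at r=0.5 and negligible at r=0.9. With a one-sided test the change-score total would be 112, but nothing in the article states one.

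This is a matter of precision and of consistency between sample size and analysis. It is not evidence of bias: with a baseline taken before treatment, the unconstrained model is unbiased under randomization.

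**What to change.** In Planned Analysis, state that for each continuous outcome with a baseline measurement, the between-arm difference at each follow-up is estimated with that outcome's baseline value as a covariate, or in a mixed model whose arm means are constrained equal at baseline.

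For body mass, define the baseline as the initial weight recorded before the diet starts, not a weekly mean that may include days on the diet. The blood baseline raises no such difficulty, since that sample is drawn before randomization.

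In Sample Size Calculation, restate the power for this test: about 79% at 61 completers per arm.

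The cost is a few sentences and one degree of freedom. Participants without a baseline value need the constrained-means version or a simple imputation. Because 49 participants were already enrolled by April 2020, the team should confirm that a pre-diet weight exists for them before fixing the definition.

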### Potential Risks and Mitigation

The potential risks of this research are minimal and relate to following a low-carbohydrate diet. As with many dietary changes, the switch to a low-carbohydrate diet can sometimes lead to headaches, nausea, or low energy. The Keyto program uses a modified ketogenic or low-carbohydrate high-fat diet which derives 70% of calories from fat. At the beginning of low-carbohydrate high-fat diets, some participants may experience transient adverse side effects including headache, light-headedness, achiness, and muscle cramps [34]. These side effects are sometimes referred to as the “keto flu [35],” appear to be related to changes in electrolytes and diuresis and can be mitigated by broth or bouillon supplementation and adequate sodium intake. The intensity of these symptoms is expected to decline as the study progresses and participants become adapted to a ketogenic diet. Possible long-term adverse side effects of ketogenic diets in adults who are overweight and obese, but otherwise healthy, are currently unknown.

## Results

The study was registered at ClinicalTrials.gov (NCT04165707). Recruitment opened December 1, 2019. The first participants began the app-based diet plan to which they were allocated on January 6, 2020. As of April 2020, there were 49 participants enrolled in the study. We expect rolling recruitment to be completed by July 2020, and the primary intervention phase to be completed 12 weeks later (October 2020), with 2 exploratory follow-up time points at 24 weeks (January 2021) and 48 weeks (July 2021).

## Discussion

Any diet is only as effective as adherence to it. Low-carbohydrate diets can be complex and challenging to adhere to [9,36], and very low–carbohydrate ketogenic diets may be even more challenging as they require greater dietary restriction to promote ketosis and sustain weight loss. Low-carbohydrate and ketogenic diets have been shown to be efficacious at promoting weight loss in structured settings [9,11,37], but maintaining them in free-living conditions may be challenging. This paper outlines the protocol for a randomized trial testing the efficacy of the Keyto breath sensor and app intervention against the WW app in promoting weight loss for 12 weeks. The Keyto intervention is delivered entirely through an app and lowers the burden of self-monitoring required to promote weight loss when following a ketogenic diet by providing an easy means of tracking ketosis using a handheld breath acetone monitor. For this reason, Keyto may be particularly effective at promoting weight loss in free-living conditions.

One potential challenge that may be encountered during the conduct of this trial is strong preferences for one of the diet conditions. Participants with strong diet preferences that are not randomized to their preferred diet may be less motivated to adhere to their allocated condition, which may influence outcomes. In real-world settings, individuals would simply choose the diet plan that they want. However, the design of a randomized trial precludes this possibility. To alleviate this potential confounder, we established eligibility criteria requiring participants to be open to both types of diets. This may constrain the generalizability of our findings to those who are most motivated. However, it is viewed as less of a confounding factor given that both interventions are mHealth products that must be purchased, so users in real-world settings would need to be motivated in order to consider either weight loss app. Furthermore, a randomized efficacy trial with strict eligibility criteria is necessary and appropriate for the stage of research [38]. The findings are generalizable to those meeting the eligibility criteria (eg, motivated adults with overweight or obesity and without comorbidity) and may not be generalizable to the entire population.

This trial will provide evidence comparing weight loss outcomes between a handheld breath ketone monitor and ketogenic diet app (Keyto) and an established caloric restriction–based weight loss app or program (Weight Watchers). The Keyto intervention may help with adherence to a ketogenic diet through direct biofeedback and personalization thereby helping to promote maintained weight loss equivalent or superior to the gold-standard weight loss app. This would provide evidence for breath ketone monitoring as an adjunct to ketogenic diets for adults with obesity who are trying to lose weight.

Research examining changes in metabolic health outcomes following ketogenic diet have typically found a differential impact on blood lipids, with potentially favorable increases in high-density lipoprotein concentrations and decreases in triglycerides observed concomitantly with a potentially unfavorable increase in low-density lipoprotein levels [19]. The heart-healthy approach used by Keyto is novel and is designed to increase consumption of plant- and fish-based foods that are higher in monounsaturated and omega-3 polyunsaturated fatty acids in order protect against an increase in low-density lipoprotein cholesterol. Exploratory blood measures will help to determine whether the heart-healthy ketogenic dietary approach results in changes in blood lipid profile (including low-density lipoprotein particle size distribution) that are favorable for cardiovascular health.

It is important to examine different strategies to combat obesity given its prevalence and adverse impacts. A ketogenic diet may be an effective strategy for weight loss; however, its success depends on adherence, and adherence to a ketogenic diet can be challenging. Furthermore, there are concerns about the potential detrimental cardiovascular effects of the high-fat intake that is promoted in ketogenic diets. This trial will provide high-quality evidence regarding whether Keyto’s version of the ketogenic diet promotes weight loss without detrimental effects on the blood lipid profile.

